### Analyses

SPSS software will be used to address the first and third hypotheses described below; Mplus software will be used to address the second hypothesis.

Hypothesis 1a: Preexposure to a stimulus will lead to diminished prediction errors in the outcome of the pre-exposed stimulus and diminished attention to the target stimulus.

The changes expected in the candidate mediators should first be observed during the pre-exposure phase. To test hypothesis 1a effects during this phase, two separate one-way repeated measures ANOVAs (with trials during the pre-exposure phase as the factor) will be run, one with attention during pre-exposure serving as the dependent variable and the second with prediction errors during pre-exposure serving as the dependent variable. To describe the change across trials, we will examine a plot of the mean responses across trials and test for the mean change from the first to the last trial in which the mediators are assessed. The Greenhouse–Geisser adjustment will be used to address possible violations of the sphericity assumption.

To examine the effects of preexposure on the candidate mediators during the conditioning phase, attention and prediction errors captured during conditioning trials will serve as dependent variables in two separate two-way (stimulus type X trial) repeated measures ANOVAs. If a significant stimulus x trial interaction is found in these analyses, stimulus type differences will be examined at each trial (using Bonferroni-adjusted alpha), and we will examine a plot of the mean response by stimulus type and trial.

In the recall and retention phases, scores on each of the candidate mediators will be averaged across trials and a one-way within-subjects ANOVA, with stimulus type as the factor, will be conducted separately for each outcome. Significant effects will be followed-up with paired samples *t*-tests to assess for specific differences between the stimulus types.

Hypothesis 1b: Pre-exposure to a stimulus will lead to decreases in fear acquisition, recall, and retention.

Inasmuch as learning effects cannot be seen until the conditioning phase, this hypothesis is tested only during the conditioning, recall, and retention phases. To test hypothesis 1b, the conditioning phase and recall and retention phase analyses described above will be conducted with indicators of fear learning (fear ratings, approach behaviour, and skin conductance response) serving as the dependent variables. In cases in which there are multiple measurements (i.e., fear ratings, skin conductance) scores will be averaged within each phase.

Hypothesis 2: Changes in prediction errors and attention will mediate the effects of pre-exposure on fear acquisition, recall, and retention.

To test the second hypothesis, three sets of multilevel mediation models [19, 20] will be estimated to test for mediation of the fear acquisition, recall, and retention effects. Each mediation analysis will include stimulus type (dummy-coded) and the two candidate mediators—prediction errors and attention.

Parameters will be obtained by maximum likelihood estimation with robust standard errors, a procedure that is robust to violations of normality and heteroscedasticity and obtains optimal parameter estimates when response data are incomplete [21, 22], with indirect effects tested by a z test. However, given the z test may be underpowered, we will double-check results by also using Bayesian estimation, which provides for improved inference via 95% credible intervals for indirect effects [23, 24].

Hypothesis 3. Higher pain sensitivity will be associated with greater engagement of the targeted mechanisms and greater LI of conditioned fear acquisition, recall, and retention.

To test the third hypothesis, individual differences in pain sensitivity will be included in the above analyses as a moderating variable.

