## Methods and analyses

### Participants and setting

Participant enrollment will occur at two university sites—one in northwest Ohio and one in south Texas. Based on a power analysis, we aim to recruit 100 participants from the general community, ranging in age from 6 to 35 years old. Full eligibility requirements are presented in Table 1. Participants will complete two in-person study visits and receive a $50 gift card at each visit completed.

**Table 1 Tab1:** Participant eligibility criteria

Inclusion criteria	Exclusion criteria
Be between the ages of 6 and 35 years old	Currently have glasses or use contact lenses with a vision correction of ≥ ± 6
At least 2 of their maxillary anterior 6 teeth present	Are colorblind
All of their maxillary anterior 6 teeth are stable	Current injury (including fractures, open cuts, or sores) on their dominant hand
All of their maxillary anterior 6 teeth are free of cavities	Fixed dental or orthodontic appliance that would interfer with creating a mouthpiece
All of their maxillary anterior 6 teeth are free of hypersensitivity to pain or pressure	Diagnosis by a dental/oral health professional of Temporomandibular Disorder (TMD) along with a history of exacerbation of symptoms resulting from routine dental procedures
Able to read, write, and converse in English (English or Spanish at Texas site)	Currently on any anti-anxiety or anti-depressant medications
Willing and able to provide a signed and dated informed consent/assent form to participate	Currently have an inner ear infection
Willing and available to comply with all study procedures and available for the duration of the study	Living in the same household or an immediate family member of an enrolled participant
	Currently have a cardiovascular disorder or a pacemaker
	Currently have a seizure disorder or epilepsy
	History of frostbite or sensitivity to extreme cold
	Bleeding disorder or take blood thinners
	Vasospastic disorder such as Raynaud's syndrome or Raynaud's disease
	Gastrointestinal or vestibular disorders that may elevate susceptibility to nausea and dizziness such as Meniere's disease, hyperemesis gravidarum or severe migraines
	Negative outcome with VR simulation
	Medical or psychological condition that requires them to avoid mild stress
	Any medical condition that elevates risk of falls, dizziness, nausea, or causes a vasovagal reaction
	Any other general or oral health concerns

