### Procedure

Although the participant will experience the “game” seamlessly, the task is broken up into four phases: pre-exposure, conditioning, and recall phases, administered during Visit 1, and a retention phase, administered during Visit 2. Each phase can be further broken down into a series of trials, which we describe next.

The *pre-exposure phase* consists of 12 trials. Each trial begins with a minimum of six seconds in which the participant is free to roam the planet using the HTC Vive Pro controllers to collect fuel hidden in the environment. At the completion of this phase of the trial an algorithm is set to deliver the CS^+^_P_, accompanied by a fuel canister, at the first opportunity.^2^ The CS^+^_P_ and the fuel canister will appear at a fixed distance from the participant. The CS^+^_P_ remains for the last six seconds of the trial. During pre-exposure, the CS^+^_P_ is never accompanied by the UCS.

The *conditioning phase* is made up of 36 trials (12 CS_P_^+^ trials, 12 CS^+^_NP_, and 12 CS^−^ trials) presented in a pseudo-random order. These trials follow the same structure as those in the pre-exposure phase with the exception that 75% of CS^+^_P_ trials, and 75% of CS^+^_NP_ are accompanied by a dental startle (described below). More specifically, the dental startle will be delivered during the last 100 ms of the trial, with the startle and alien co-terminating. The CS^−^ is never presented with the dental startle.

In the fear *recall phase* 12 trials (4 CS^+^_P_ trials, 4 CS^+^_NP_, and 4 CS^−^ trials) are presented. Again, these trials follow the structure described in the pre-exposure and conditioning phases; however, none of the aliens are presented with the UCS.

Fear retention will be assessed in the *retention phase*—a repeat of the recall phase administered a minimum of 7 days later.

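### The trial-level ANOVAs fixed for eye-tracking attention (Hypotheses 1a and 3) drop any participant with one missing trial, whereas the Hypothesis 2 method keeps incomplete records

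*Protocol article*

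**What the plan says.** All references are to the protocol article.

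- **Software (Analyses).** "SPSS software will be used to address the first and third hypotheses described below"; Mplus is reserved for the second.
- **Pre-exposure, Hypothesis 1a (Analyses).** For attention and for prediction errors, "two separate one-way repeated measures ANOVAs (with trials during the pre-exposure phase as the factor) will be run". The Greenhouse–Geisser adjustment is named here. The Procedure section says this phase "consists of 12 trials".
- **Conditioning, Hypothesis 1a (Analyses).** The same two mediators are analysed "in two separate two-way (stimulus type X trial) repeated measures ANOVAs". The phase "is made up of 36 trials", 12 for each of the three stimuli.
- **Recall and retention (Analyses).** Here "scores on each of the candidate mediators will be averaged across trials and a one-way within-subjects ANOVA, with stimulus type as the factor" is used, so trials are collapsed before the test.
- **Hypothesis 1b (Analyses).** The conditioning, recall and retention analyses are carried over to the fear indicators. Fear ratings and skin conductance are then said to be averaged within each phase.
- **Hypothesis 2 (Analyses).** Multilevel mediation models are estimated by maximum likelihood with robust standard errors, a procedure that "obtains optimal parameter estimates when response data are incomplete".
- **Hypothesis 3 (Analyses).** Pain sensitivity enters the analyses already described, as a moderator.
- **Measures and Discussion.** Attention is eye-tracking dwell time. Ratings are intermittent. The shortest distance to each alien is logged on every trial.

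**The concern.** A classical repeated-measures ANOVA in SPSS takes one row per participant and one column per cell, and uses only rows with every cell filled. Naming Greenhouse–Geisser points to that procedure rather than to a mixed model. A participant with 35 valid dwell times out of 36 in conditioning would contribute nothing to that ANOVA, nor to its Hypothesis 3 version.

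Dwell time is the measure for which this matters most, because it depends on usable eye tracking in a headset while participants, some as young as 6, move freely. Two things are at stake.

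- **Precision.** The attention tests may rest on fewer than the recruited participants.
- **Coherence.** Attention is the Hypothesis 1a outcome and also a Hypothesis 2 mediator. If 1a uses complete records and 2 uses all records, the effect of pre-exposure on attention and the part of the fear effect carried by attention may be estimated in different sets of people.

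This is not a complaint about missing detail. The method is stated, and it suits this outcome poorly.

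**Working it through.** **The plan's own figure.** "Based on a power analysis, we aim to recruit 100 participants from the general community". The article does not give the alpha, power, effect size or dropout behind this number, so 100 cannot be reproduced. It serves below only as the starting sample.

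**Which analyses need complete trials**

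| Outcome and phase | Cells per person | Exposed to single-trial deletion? |
|---|---|---|
| Attention, pre-exposure | up to 12 | yes |
| Attention, conditioning | up to 3 x 12 = 36 | yes |
| Prediction errors, pre-exposure and conditioning | fewer, as ratings are intermittent | yes, to a lesser degree |
| Approach distance, conditioning | up to 36 | same structure; no sign in the article that it is prone to loss |
| Skin conductance, fear ratings | averaged within phase | largely not |
| Recall and retention | 3 stimulus means | largely not |

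**Share with complete records.** The article gives no trial-loss rate, so the per-trial loss p is an assumption (1%, 2%, 5%).

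- Independent losses: share complete = (1 − p)^k, with k cells.
- Losses clustered within people (beta-binomial, within-person correlation ρ): share complete = B(a, b + k) / B(a, b), where B is the beta function, a = p(1 − ρ)/ρ and b = (1 − p)(1 − ρ)/ρ.

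For k = 36, independent: 0.99^36 = 0.696; 0.98^36 = 0.483; 0.95^36 = 0.158.
For k = 12, independent: 0.99^12 = 0.886; 0.98^12 = 0.785; 0.95^12 = 0.540.

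Example with clustering: p = 0.02 and ρ = 0.1 give a = 0.18 and b = 8.82, hence 0.741 for k = 36.

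| Assumed loss per trial | 36 cells, independent | 36 cells, ρ = 0.1 | 36 cells, ρ = 0.3 | 36 cells, ρ = 0.5 | 12 cells, independent |
|---|---|---|---|---|---|
| 1% | 70% | 86% | 93% | 96% | 89% |
| 2% | 48% | 74% | 87% | 92% | 78% |
| 5% | 16% | 47% | 70% | 81% | 54% |

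**What averaging does.** If scores are averaged over the available trials, a person is lost only when every trial of some stimulus is missing. At 5% independent loss that probability is about 3 x 0.05^12, below 10^-14, with 12 trials per stimulus, and about 3 x 0.05^4 = 0.00002 with 4. This is why the averaged analyses are not part of the point.

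**Rough scale of the power loss.** This is an illustration, not the plan's calculation. Suppose 100 participants gave 80% power for a two-sided 5% paired contrast, which corresponds to a standardised effect of 0.283. By the noncentral t distribution, power would then be 77% at n = 92, 71% at 81, 65% at 70, 48% at 48 and 18% at 16.

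**The case against.** **The loss rate is unknown, and so is what counts as a missing dwell time.** The alien is on view for six seconds. A brief tracking dropout need not void the trial, and not looking at the alien may be a valid zero. The rule may well be in the full protocol or analysis plan, so its absence here is no fault. This stands: the size of the loss cannot be stated, only its range.

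**Losses probably cluster.** Poor tracking tends to belong to particular people, and clustering softens the loss considerably. This also stands, and it is why the independent column is the pessimistic end. Clustering does not remove the concern. It shifts it from lost precision towards who is left out.

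**Stronger readings.** A reader might infer any of the following, and the article supports none of them.

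- *That skin-conductance loss also removes participants.* Those scores are averaged within phase. That sentence sits awkwardly with the stimulus-by-trial analysis carried over to Hypothesis 1b and deserves clarifying, but it gives no ground for single-trial deletion.
- *That all of Hypotheses 1 and 3 is affected.* Recall and retention use averages throughout.
- *That distance in the virtual environment is prone to loss.* It is recorded on each trial, and nothing suggests gaps.
- *That the authors forecast incomplete data.* The Hypothesis 2 text describes a property of the estimator and makes no forecast.
- *That those retained would be older, calmer or less avoidant.* This is plausible, but the article has no data on it.
- *That much of the 100 would be lost.* That is one corner of a wide range.

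**The power figures are for a paired t-test.** The paired t-tests that the plan names follow the averaged recall and retention analyses, so these figures indicate scale only.

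**Conclusion.** The point holds for eye-tracking attention in the pre-exposure and conditioning phases, under Hypothesis 1a and the corresponding Hypothesis 3 analyses. The stated method needs a complete set of up to 12 or 36 trials per person, while the Hypothesis 2 method in the same section does not. Prediction-error ratings share the weakness with fewer cells. Approach distance shares the structure without evidence of loss.

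The size is conditional. At assumed losses of 1% to 5% per trial, complete 36-cell records range from 96% of participants (1%, ρ = 0.5) down to 16% (5%, independent). The conclusion rests on the standard complete-case SPSS procedure being meant, which the wording and the sphericity correction indicate, and on at least some dwell-time cells being missing. The change is worth making because it is cheap and protects against the bad end of the range, not because a large loss has been shown.

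**What to change.** Make a linear mixed model on all available trials (SPSS MIXED) the primary analysis for the outcomes analysed by trial in pre-exposure and conditioning under Hypotheses 1 and 3.

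- **Fixed effects:** trial in pre-exposure; stimulus, trial and their interaction in conditioning. For Hypothesis 3, add pain sensitivity and its interactions with these terms.
- **Covariance:** prespecified, with participant and participant-by-stimulus effects (participant only in pre-exposure, where there is one stimulus).
- **Sensitivity analysis:** keep the planned repeated-measures ANOVA as a complete-case analysis, and report how many participants it retains.

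The averaged recall and retention analyses need no change on this account.

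The cost is a change of analysis wording, with the same data and software. There are two drawbacks. The covariance structure must be chosen in advance, and validity rests on trials being missing at random given the observed data. That is weaker than what the complete-case ANOVA needs, but it could still fail if tracking is lost because of where the participant is looking.

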#### Stimuli

##### Aliens

Three novel aliens will serve as the CS_P_^+^, CS_NP_^+^, and CS^−^. The aliens were created for the project to ensure novelty and selected based on piloting with children, adolescents and adults which showed them to be perceived similarly and as relatively neutral; nevertheless, counterbalancing procedures will be used to rule out any stimulus-specific effects.

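### In the conditioning phase, pre-exposed and non-pre-exposed stimuli are compared only behind a three-stimulus interaction, trial by trial at Bonferroni alpha, which costs power for the effect Hypothesis 1 is about

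*Protocol article*

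**What the plan says.** All references are to the protocol article.

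- **Design (Procedure).** "The *conditioning phase* is made up of 36 trials", 12 for each of three stimuli. Of the CS+P and of the CS+NP trials, 75% "are accompanied by a dental startle"; the CS- "is never presented with the dental startle".
- **Conditioning-phase test (Analyses, Hypothesis 1a).** Attention and prediction errors each go into a two-way stimulus type by trial repeated measures ANOVA. The decision rule is: "If a significant stimulus x trial interaction is found in these analyses, stimulus type differences will be examined at each trial (using Bonferroni-adjusted alpha"), together with a plot of means. Nothing is stated for a significant stimulus main effect without an interaction.
- **Recall and retention (same section).** After averaging over trials, "a one-way within-subjects ANOVA, with stimulus type as the factor, will be conducted separately for each outcome". Significant results are followed by paired t-tests between stimuli.
- **Hypothesis 1b (same section).** The same analyses are repeated with the fear indicators ("fear ratings, approach behaviour, and skin conductance response) serving as the dependent variables"). The next sentence says that fear ratings and skin conductance are averaged within each phase.
- **Sample size (Participants and setting).** "Based on a power analysis, we aim to recruit 100 participants from the general community".

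**The concern.** Hypothesis 1 is about what pre-exposure does. CS+P and CS+NP share a reinforcement schedule and differ in pre-exposure. CS- differs from both in reinforcement. An F test over all three stimuli therefore mixes two questions: whether conditioning happened, and whether pre-exposure slowed it. The first can carry the test alone.

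The comparison that answers the second question is made only if this mixed test is significant, and then in pieces, each with the information of one trial and a reduced alpha. A real pre-exposure effect spread thinly over the phase may pass at no single trial. One that is about the same at every trial adds nothing to the interaction, so it does not help to open the gate. Fear acquisition is one of the three outcomes in every hypothesis, and Hypothesis 3 adds a moderator to these same analyses, so the weakness carries forward.

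**Working it through.** **Inputs from the article.** 100 participants, within-subject; three stimuli; 12 conditioning trials per stimulus; Greenhouse-Geisser adjustment. Ratings are intermittent (Discussion), so rated trials number fewer than 12 per stimulus; how many is not given. The Bonferroni family is not stated, so 12 tests (one per trial) and 36 (three pairs by 12 trials) are both shown.

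**The plan's own figure.** The target of 100 can be neither reproduced nor refuted, because the article gives no effect size, SD, alpha or power. That is not a finding here. For orientation, the paired standardised effect dz detectable with 80% power at two-sided 0.05 is (1.96 + 0.84)/√100 = 0.28.

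**Step 1: cost of testing at one trial.** The same formula gives 0.37 at 0.05/12 and 0.40 at 0.05/36. Holding 0.28 per trial would need about 100 × (0.3707/0.2802)² = 175 or 100 × (0.4039/0.2802)² = 208 participants. Exact noncentral-t power at dz = 0.30, n = 100:

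| alpha | power |
|---|---|
| 0.05 | 84% |
| 0.05/12 | 53% |
| 0.05/36 | 39% |

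**Step 2: what the interaction responds to.** Simulation of the stated procedure with CS+P and CS+NP identical (no latent inhibition). Assumed: total SD 1, person variance 0.5, person-by-stimulus variance 0 or 0.1, exponential learning to both CS+ starting from zero, flat CS-, 12 or 4 trials, 1,000 runs per cell.

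| Conditioning at asymptote | Interaction significant |
|---|---|
| 0.3 SD | 41-56% |
| 0.5 SD | 90-99% |
| 0.8 SD | 100% |

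In the same runs, at least one trial-wise CS+P vs CS+NP test is falsely significant in about 3-6% (Bonferroni over trials) or 1-2% (over trials and pairs).

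**Step 3: power for a real effect.** Same model, 12 trials, conditioning 0.5 SD, latent inhibition 0.2 SD: the planned phase-average contrast has 78% to >99% power. The gated route finds at least one significant trial in 60-65% (0.05/12) or 43-45% (0.05/36). With conditioning of 0.3 SD and the same latent inhibition, the gate opens in only 30-43% of runs, while the planned contrast has 79% to >99%.

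A second model: residual SD 1, person-by-stimulus SD 0.5, asymptote 0.6, learning rate 0.10 for CS+P and 0.30 for CS+NP. The planned contrast can be checked by hand with curves 0.6(1 − e^(−rt)), t = 0 to 11:

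- Average of e^(−rt): (1 − e^(−3.6))/(12(1 − e^(−0.3))) = 0.313 for r = 0.30; (1 − e^(−1.2))/(12(1 − e^(−0.1))) = 0.612 for r = 0.10.
- Mean difference: 0.6 × (0.612 − 0.313) = 0.18.
- SD of the phase-average difference: √(2(0.25 + 1/12)) = 0.816, so dz = 0.22 and power is about 59%.
- At a single trial the largest difference is 0.6(e^(−0.5) − e^(−1.5)) = 0.23. The SD is √(2(0.25 + 1)) = 1.58, so dz = 0.15, far below the 0.37 or 0.40 of Step 1.

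Two simulations of this scenario gave 29% and 34% for the gated route at 0.05/12, 17% and 18% at 0.05/36, and 58% and 61% for the planned contrast.

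**Step 4: a constant shift.** Take CS+P lower than CS+NP by 0.3 at every trial, with no interaction present. The planned contrast has dz = 0.3/0.816 = 0.37 and power of about 95% (96% simulated). The gated route finds it in 3%, because the gate opens only by chance. If conditioning itself drives the interaction, the gate can open and the loss is smaller.

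**Step 5: Hypothesis 1b.** One sentence carries the stimulus by trial analysis over to all fear indicators. The next averages fear ratings and skin conductance within each phase, which leaves no trial factor. Both cannot hold for these two indicators. The trial-wise route therefore applies literally to attention, prediction errors and trial-wise approach behaviour. If averaging governs the other two, their test is still a three-stimulus omnibus that conditioning alone can make significant.

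**The case against.** Several objections have weight.

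- **A reader might infer that the plan would declare latent inhibition from the omnibus F.** The article does not say so. It labels no F as primary and follows the F with stimulus comparisons and a plot. Step 2 shows that those comparisons control false positives. The defect is in power.
- **A reader might extend the point to all three phases.** Recall and retention reach paired t-tests on averaged scores, and a three-level omnibus in front of them costs little. Simulated on phase averages, the gated and ungated contrasts both had 60% power at asymptote 0.6 and both 96% at 1.0; at 0.3 they had 17% against 20%.
- **The percentages rest on assumed effects.** This stands. With no latent inhibition and a 0.6 asymptote, the interaction was significant in 79-83% of runs when learning is zero at the first presentation. It fell to 47% if learning starts one step later and to 26% with four rated trials. With asymptote 1.0 the gated route finds the effect in 86% (0.05/12) or 68% (0.05/36). In one cell (four trials, person-by-stimulus variance 0.1, conditioning 0.8 SD, latent inhibition 0.3 SD) it slightly beat the planned contrast, 83% against 81%.
- **Other analyses may supply the contrast.** The mediation models enter dummy-coded stimulus type without an ANOVA gate, but the reference category is not named and they address Hypothesis 2. The pre-exposure phase shows only CS+P, so it holds no such comparison.
- **Error control across the fear indicators** might also be raised, but an article may leave that to the analysis plan, and it is no part of this point.

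**Conclusion.** The point holds for the conditioning phase, for attention, prediction errors and trial-wise approach behaviour. The stated decision rule gives the one contrast that isolates pre-exposure no phase-level test, puts it behind an interaction that CS+ against CS- learning can drive, and leaves a stimulus main effect without follow-up. This is a rule the article commits to, so it is not detail left to another document.

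The consequence is lost power for Hypothesis 1: about 17-34% against about 60% in the 0.6 SD scenario, and 43-65% against 78% or more with 0.5 SD conditioning and 0.2 SD latent inhibition. Both rest on assumed variances, learning curves and an assumed Bonferroni family. The direction held in nearly all scenarios run; the size is not known for this trial. The documents do not support saying that the omnibus is significant whenever conditioning occurs, that a true effect will usually be missed, or that recall and retention are materially affected.

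**What to change.** - For each outcome in the conditioning phase, name one planned CS+P vs CS+NP contrast on the phase average, two-sided at 0.05, tested whatever the omnibus shows. The phase average should be named explicitly: the two-stimulus interaction with trial alone had only 11-61% power in the scenarios run with latent inhibition of 0.15 to 0.3 SD.
- Keep that contrast's interaction with trial as secondary, and CS+NP vs CS- as the check that conditioning occurred.
- Present per-trial comparisons descriptively, with the planned plot.
- Use the same direct contrast in recall and retention, for consistency.
- Reconcile the two Hypothesis 1b sentences: state for each fear indicator whether it is analysed by trial or as a phase average.

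The cost is wording only, with no new data, participants or procedures. The downside is that per-trial p values lose confirmatory status.

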### Study design and overview of procedures

Study variables include one measured subject variable (pain sensitivity) and two within-subjects manipulated variables [stimulus type: pre-exposed to-be conditioned stimulus (CS^+^_P_), non- pre-exposed to-be conditioned stimulus (CS_NP_^+^), and a never-conditioned stimulus (CS^−^)] and time [trial number].

After providing verbal consent, potential participants^1^ will complete a phone screen to assess eligibility. Interested participants meeting criteria will then participate in two study visits, approximately one week apart (min = 7 days,). Each visit will last approximately 90 min.

Visit 1 will begin with the completion of the consent and assent (if applicable) process, and confirmation of eligibility. Participants will then complete the measures and behavioural tasks described below as well as the experimental task. During the experimental task, the pre-exposure intervention will be administered, and fear conditioning procedures will be conducted. Immediately following, conditioned fear recall will be assessed; a minimum of 7 days later, fear retention will be assessed at Visit 2.

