#### Indicators of fear learning

Data on subjective, behavioral, and physical indicators of fear learning will be assessed. Participants provide ratings of their state of relaxation/anxiety when in the presence of the CS^+^_P_, CS^+^_NP_, and CS^−^ periodically throughout the experimental task. Additionally, approach behavior will be quantified in two ways; the shortest distance between the participant and the CS^+^_P_, CS^+^_NP_, and CS^−^ will be recorded on each trial as will the data on whether or not the participant collected the “fuel cell” in proximity the CS^+^_P_, CS^+^_NP_, and CS^−^. Finally, skin conductance response to the CS^+^_P_, CS^+^_NP_, and CS^−^ presentations will be recorded using two Ag–AgCl electrodermal conductance electrodes with Isotonic gel placed on the middle phalanges of the non-dominant hand ring and pinky fingers. Data from the electrodes will be recorded using Biopac MP160 with a wireless BioNomadix module transmitter (Biopac Systems, California, USA.), with a sample rate of 2000 Hz, using Biopac’s Acknowledge 5.0 software (Biopac Systems, California, USA.). Skin conductance data will be analyzed based on prior work [16].

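### The stated Hypothesis 2 mediation model has no trial term, so if the acquisition models use trial-level scores, time courses common to mediator and outcome can appear as mediation

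*Protocol article*

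**What the plan says.** All of this is in the Protocol article.

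- **Hypothesis 2 (Analyses).** The plan is that "three sets of multilevel mediation models [19, 20] will be estimated to test for mediation of the fear acquisition, recall, and retention effects". Their content is given as "Each mediation analysis will include stimulus type (dummy-coded) and the two candidate mediators—prediction errors and attention". Estimation is by maximum likelihood with robust standard errors, "with indirect effects tested by a z test", and a Bayesian fit serves as a check. Neither trial nor the unit of a data row is mentioned.
- **Design (Study design and overview of procedures).** Besides stimulus type, the within-subject variables include time: "and time [trial number".
- **Hypothesis 1a (Analyses).** In conditioning, the mediators go into "two separate two-way (stimulus type X trial) repeated measures ANOVAs". In pre-exposure the plan will "test for the mean change from the first to the last trial in which the mediators are assessed", so change over trials is expected there. In recall and retention the mediators are averaged over trials.
- **Hypothesis 1b (Analyses).** Repeated measurements are averaged within phase. The sentence names fear ratings and skin conductance, not approach behaviour.
- **Indicators of fear learning.** The closest distance to each alien "will be recorded on each trial as will the data on whether or not the participant collected" the fuel cell.
- **Procedure.** Conditioning has 36 trials, 12 per alien. CS+ aliens are paired with the startle on 75% of their trials, and the CS− alien never is.

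**The concern.** For trial-level rows, the stated model reads: mediator = person + stimulus dummies; outcome = person + stimulus dummies + prediction errors + attention. Attention and approach distance may both change over 36 trials through practice, fatigue or habituation. Without a trial term, two measures that drift over the same trials are correlated within person even if neither influences the other. That correlation is absorbed by the mediator-to-outcome coefficient (b). Multiplied by a real stimulus effect on the mediator (a), which Hypothesis 1a predicts, it gives a non-zero indirect effect.

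Robust standard errors do not help, because the coefficient itself is biased. The Bayesian check is described as a second estimation of the same analysis, so it would carry the same bias. Hypothesis 2 is the study's mechanistic claim, and the Discussion says that the results could guide prevention programmes.

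**Working it through.** The article gives no effect size, SD, alpha or drift, so there is no figure of the plan to reproduce.

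**Inputs from the article:** 100 participants, three aliens, 36 conditioning trials (12 per alien), z test of the indirect effect.

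**Assumptions:** two-sided alpha 0.05; residual SD 1; person-intercept SD 0.7; a = −0.3 SD for CS+P versus CS+NP; true b = 0; one mediator, observed on every trial; linear drift of d SD from start to end of the phase in both mediator and outcome.

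**Approximate size of the false b.** Let t run from −0.5 to 0.5 over K = 36 trials. Its sum of squares per person is

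S = K(K² − 1) / [12(K − 1)²] = 36 × 1295 / (12 × 1225) = 3.171.

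After removing person means, b without a trial term is about d²S / (K − 1 + d²S). Its standard error is about 1/√(100 × 35) = 0.0169.

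| d (SD) | false b | b / SE |
|---|---|---|
| 0.3 | 0.285 / 35.285 = 0.008 | 0.5 |
| 0.5 | 0.793 / 35.793 = 0.022 | 1.3 |
| 0.8 | 2.030 / 37.030 = 0.055 | 3.2 |
| 1.0 | 3.171 / 38.171 = 0.083 | 4.9 |

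At d = 1 the false indirect effect is about −0.3 × 0.083 = −0.025.

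**Simulation.** 500 runs per row, within-person regressions, person-clustered robust standard errors, delta-method z test of a × b. Entries are the percentage of studies with a significant indirect effect although b = 0. The Monte Carlo error near 5% is about 1 point.

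| Drift shared by all aliens | No trial term | Trial only | Trial and stimulus x trial | Phase means |
|---|---|---|---|---|
| 0 | 4.8 | 4.8 | 4.8 | 3.6 |
| 0.3 | 5.6 | 3.2 | 3.4 | 5.0 |
| 0.5 | 21.6 | 5.2 | 5.2 | 4.4 |
| 0.8 | 90.4 | 3.4 | 3.0 | 4.4 |
| 1.0 | 100 | 6.0 | 6.4 | 4.4 |

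Repeat runs, some with an added person-by-alien SD of 0.3, gave 20 to 22%, 87 to 88% and 99 to 100% at 0.5, 0.8 and 1.0 SD without a trial term. The simulated mean b matches the formula: 0.023, 0.055 and 0.084.

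**When aliens drift differently.** Only the CS+ aliens are paired with the startle, so their time courses should differ from that of the CS− alien.

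| CS− time course | CS+ drift | No trial term | Trial only | Trial and stimulus x trial | Phase means |
|---|---|---|---|---|---|
| flat | 0.8 | 52.4 | 9.0 | 3.6 | 5.6 |
| flat | 1.0 | 91.2 | 18.2 | 3.8 | 4.0 |
| opposite | 0.8 | 90.4 | 81.0 | 4.2 | 4.8 |
| opposite | 1.0 | 99.8 | 97.8 | 4.4 | 3.6 |

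**Conditions for the error (12 trials per alien, 1 SD drift).** If only the mediator drifts, the rate is 4.4%. If both drift but a = 0, b is still false (0.082), yet the indirect effect is significant in only 2.8%.

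**Fewer usable trials.** With 4 trials per alien and no trial term, the rate is 8 to 12% at 0.5 SD and 81 to 89% at 1.0 SD.

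**The case against.** The strongest reply is that the article never says Hypothesis 2 uses trial-level rows. The averaging it does state covers fear ratings and skin conductance within phase, and the mediators in recall and retention. A model with three aliens nested in each person is still multilevel. This stands as a limit on scope. It does not settle the matter, because those rules sit under Hypothesis 1, the conditioning-phase mediators are analysed by trial, and approach behaviour is not named among the averaged scores. One could read the averaging sentence as covering approach behaviour too, since it is also measured repeatedly, but its bracket lists only the other two.

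Second, the Discussion says that ratings are intermittent. Prediction errors are ratings, so complete rows on all 12 trials per alien are not planned. This stands: fewer rows weaken the effect, and the number of rated trials is not given.

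Third, an article condenses the plan, and a list of what a model will include need not be complete. That is fair, and the full plan may name trial. Still, the one model statement given leaves out a factor that the article declares and uses for Hypothesis 1.

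A reader might infer that mediation will be falsely reported across all three phases and every fear indicator. The article does not support that. Trial-level rows are not stated, recall and retention mediators are averaged, and the error needs substantial drift in both mediator and outcome together with a real stimulus effect on the mediator.

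**Conclusion.** The point holds conditionally. The stated Hypothesis 2 model omits trial, and the unit of analysis is left open. If acquisition is modelled on trial-level scores, most plainly approach behaviour, the indirect-effect test can report mediation that does not exist. The size depends on a drift that the article does not give: negligible at about 0.3 SD or less, about 20% false positives at 0.5 SD, and severe from 0.8 SD. These rates assume linear drift, 12 complete trials per alien and a = 0.3 SD. Analyses that use phase averages for both mediators and outcome are outside the concern.

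**What to change.** State the unit of analysis for each Hypothesis 2 model, then do one of the following.

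1. Fit the model to phase means per alien for both mediators and the outcome. No trial term is then needed.
2. For any model on trial-level scores, include centred trial and stimulus x trial, the same two factors as in the conditioning-phase ANOVAs, in both the mediator and the outcome equations. A trial main effect alone leaves 9 to 18% false positives at 0.8 to 1.0 SD when the CS− course is flat, and 81 to 98% when it is opposite.

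The cost of the second option is a few within-level covariates in the Mplus models and no new data. The stimulus-to-mediator path is then read at the centred trial, and b rests on departures from each alien's own time course. The first option gives up the trial-to-trial information.
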